## Abstract

**Background:**

In patients with advanced, incurable cancer, anticancer treatment may be used to alleviate cancer-related symptoms, but monitoring of them in daily practice is rarely done. We aim to test the effectiveness of a real-time symptom and syndrome assessment using the E-MO*S*AIC software installed in handheld computer generating a longitudinal monitoring sheet (LoMoS) provided to the oncologists in a phase III setting.

**Methods:**

In this prospective multicentre cluster randomized phase-III trial patients with any incurable solid tumor and having defined cancer related symptoms, who receive new outpatient chemotherapy in palliative intention (expected tumor-size response rate ≤20%) are eligible. Immediately before the weekly visit to oncologists, all patients complete with nurse assistance the E-MO*S*AIC Assessment: Edmonton Symptom Assessment Scale, ≤3 additional symptoms, estimated nutritional intake, body weight, Karnofsky and medications for pain and cachexia. Experienced oncologists will be randomized to receive the LoMoS or not. To minimize contamination, LoMoS are removed from the medical charts after visits. Primary endpoint is the difference in global quality of life (items 29 & 30 of EORTC-QlQ-C30) between baseline and last study visit at week 6, with a 10 point between-arm difference considered to be clinically relevant. 20 clusters (=oncologists) per treatment arm with 4–8 patients each are aimed for to achieve a significance level of 5% and a power of 80% in a mixed model approach. Selected co- variables are included in the model for adjustment. Secondary endpoints include patient-perceived patient-physician communication symptom burden over time, and oncologists’ symptom management performance (predefined thresholds of symptoms compared to oncologists’ pharmacological, diagnostic or counselling actions [structured chart review]).

**Discussion:**

This trial will contribute to the research question, whether structured, longitudinal monitoring of patients’ multidimensional symptoms, indicators for symptom management, and clinical benefit outcomes can influence patients’ quality of life and symptom distress, in a setting of routine oncology practice.

**Trial registration:**

Current Controlled Trials NCT00477919

## Background

In patients with advanced, incurable cancer, anticancer treatment may alleviate patients’ cancer-related symptoms and cancer-associated complications [1]. These beneficial effects may occur even in the absence of a tumor response [2]. In contrast, reduction of tumor size does not necessarily imply a benefit to patients [3]. Chemotherapy may cause physical and psychosocial side effects [4]. An important focus of treatment is therefore to have a beneficial impact on health-related quality of life (HRQL) [5]. HRQL was reported by health care professionals [6] and medical oncologists [7] to be the most important outcome in assessing the effect of palliative chemotherapy. However, HRQL considerations rated by physicians after consultation were poorly associated with decisions regarding modification of palliative chemotherapy [8].

While both monitoring of tumor response and toxicity are defined by gold standards (i.e., RECIST, CTCAE v3.0), symptoms and syndromes, also conceptualized as patient-reported outcomes (PROs), are yet only partially incorporated in routine oncology care [9,10]. Symptoms, which are subjective perceptions of patients, cannot be measured by currently used toxicity scales [11]. Syndromes are mainly clinically described patterns, a combination of symptoms and clinical signs. Cachexia for instance is the combination of the sign weight loss and the symptom anorexia [12].

It is often assumed that an oncologist can estimate the symptoms of the patient accurately using a regular history. However, oncologists’ perceptions may differ from patients’ reported physical and psychosocial experiences. In patients with advanced cancer, the assessment of relevant psychological domains, but also of pain, asthenia/fatigue, or nutritional problems are often underestimated [13,14]. They may not be detected (lack of screening), not be quantified by the patient or by a professional (lack of measuring individuals’ symptom distress) [15,16] or their impact on patients’ everyday functioning is not taken into account (lack of estimation of the magnitude of the problem). Physicians’ concerns about time constraints arising from dealing with unexpected or complex symptoms may contribute to underestimation of symptoms, [17]. In Switzerland, an average of 15 minutes of consultation time is general practice [18].

For the monitoring of anticancer treatment, the palliative effect of chemotherapy on disease-related symptoms and syndromes [15] has been operationalized by defining a clinical benefit criterion. In pancreatic cancer, the endpoint of clinical benefit response (a composite assessment of pain, performance status and weight) was created to provide a way in which the impact of therapy on tumor-related symptoms could be assessed [19] and has become a well-accepted outcome parameter. However, outside of clinical studies its application in routine care is limited. It can therefore be hypothesized, that monitoring of both symptoms, clinical benefit parameters (as objective indicators of effect of management) and selected interventions may result in a quality of life benefit for patients.

There are several approaches pursued to bring patients’ experiences and wishes to the oncology routine care including collection of patients’ symptoms [20], palliative care needs [21], review of systems [22], or general concerns and questions [23], immediately before the visits with physicians and/or nurses. These studies document the proof of concept, that such monitoring can be applied in clinical practice. Looking at the three elements, i.e. symptoms, clinical benefit and treatments, reveals selected documented effects. Monitoring of patients’ symptoms alone increases professionals’ awareness, patient and caregiver’s satisfaction about communication, but rarely effectiveness of symptom management [24]. Monitoring of indicators of patients’ needs, such as declining physical function, distress, repeated hospitalizations, or pre-defined thresholds of symptoms alone will trigger “only” further assessment [14]. Monitoring of current treatments (e.g. pain medications) is only effective, or general concerns and questions [23], immediately before the visits with physicians and/or nurses. These studies document the proof of concept that such monitoring can be applied in clinical practice. Monitoring of patients’ symptoms alone increases professionals’ awareness, patient and caregiver’s satisfaction about communication, but rarely effectiveness of symptom management [24].

The feasibility of self-assessments in patients with advanced, incurable cancer has been demonstrated for various symptom assessment instruments, including the Edmonton Symptom Assessment Scale (ESAS) validated also in cancer outpatient clinics [25].

This study evaluates the effects of the E-MOSAIC intervention, a handheld computer-based assessment of patients’ symptoms, clinical benefit parameters and symptom management information, delivered real-time by the longitudinal monitoring sheet (LoMoS) to oncologists treating patients with anticancer treatment for advanced cancer in palliative intention.

## Methods

This study investigates the effect of E-MOSAIC delivered to oncologists on patient outcomes during a 6 week treatment duration applying a cluster-randomized controlled design.

### Development of intervention tool

Patients with incurable cancer have a high prevalence of symptoms, making it difficult to identify those symptoms essential for routine assessment. Therefore, we decided to select and group the most important symptoms and syndromes into clusters, aiming to maintain an adequate coverage of all important items. This approach should guide the treating physician in a replicable and structured way to monitor relevant (physical and psychological) symptoms and syndromes.

The E-MOSAIC intervention was developed based on pilot work monitoring both symptoms and clinical benefit parameter in oncology care, using paper and pencil to color bars from zero to ten. For symptom assessment, the Edmonton Symptom Assessment Scale (ESAS) is used [26]. The ESAS is a validated nine-item patient-rated symptom visual analogue scale developed for use in assessing the symptoms of patients receiving palliative care. The single item depression of the ESAS can reliably screen for depression as measured by more in depth instrument [27].

From published lists of frequent symptoms the study team selected 21, a number considered both feasible to be utilized in practice and comprehensive enough [28].

As next step the E-MOSAIC software was developed, piloted and refined with professionals and patients resulting in the palm-based assessment E-MOSAIC (Figure 1).

**Figure 1 F1:**
[figure not shown]
Screenshot from Palm as illustration.

The palm-based assessment consists of three elements (see screenshots in the Appendix), which are filled out by the patient (element P) and the study personnel (elements G [weight] and M [medication]).

Element P Visual-Analogue Scales (VAS) of

1. Nine frequent symptoms from ESAS (pain, fatigue, drowsiness, nausea, anxiety, depression, shortness of breath, loss of appetite, overall well-being);

For E-MOSAIC the single symptoms of the original ESAS were translated in German, French and Italian language in an informal back- and forward process, and validated preliminarily. ESAS is measured by palm in all patients.

2. Up to three optional symptoms;

3. Patients’ estimated nutritional intake.

Element G:

1. Body weight;

2. Karnofsky Performance Status;

3. Weight loss and body height (Body Mass Index calculated automatically).

Element M: pre-defined, simplified list for actual medication for:

1. Pain syndromes, including assessment of MEDD (Morphin Equivalent [oral] Daily Dose);

2. Fatigue syndromes (Methylphenidate, Erythropoietin, transfusions);

3. Anorexia/cachexia syndromes, and for edema (to control for weight changes).

After completion of the assessments the palm is put back to the docking station and the data are transferred within a few seconds from the docking station to the local computer.

The source-code of the E-MOSAIC software is copy-protected. The software is study-specific, but may be used for other purposes.

Longitudinal Monitoring Sheet LoMoS which is printed immediately and put in the patient file for the physicians’ visit by the nurse (Figure 2).

**Figure 2 F2:**
[figure not shown]
Longitudinal monitoring Sheet: LoMoS.

Structure of LoMoS:

1. VAS pain, pain medication (opioids calculated as morphine-equivalent daily dose; other analgesics);

2. VAS fatigue, KPS, medication for fatigue (Methylphenidate, Erythropoietin);

3. VAS anorexia, VAS perceived nutritional intake, weight change, medication for anorexia (nutritional counselling, progestins, prokinetics);

4. 6 ESAS symptoms

5. Maximal 3 of 21 symptoms selected by patient at baseline.

After refining the software, a formal feasibility study was performed as briefly summarized below.

Four centers participated in all or parts of the E-MOSAIC-Feasibility-Study.

Patients filled in the E-MOSAIC in a paper-pen and a palm version in random order.

The compliance, time needed, and experiences of patients with the palm were assessed by a structured 2-page evaluation.

62 patients (median age 64y [30–85], 25 female) participated. 4 patients had visual impairment, 6 comprehension problems, and 1 pat was too tired. 3/62 patients did not complete E-MOSAIC.

Median time to complete was 3 minutes. 10 patients preferred paper and 28 palm, 16 had no preference; 50 patients agreed to continue using palm.

Palm-based symptoms (VAS) were compared with a paper-based categorical symptom assessment (ESAS). Wilcoxon signed-rank tests showed no significant differences between palm and paper of 9 symptoms of element P (p-value: well-being 0.089, dyspnea 0.060, the remaining 7 symptoms 0.249-0.940), but for nutritional intake different (a significant difference was found (.p = 0.013).

Test-retest (1 hour, n = 20) reliability of 9 symptoms and nutritional intake was satisfactory (Cronbach alpha 0.62 - 0.94).

### The E-MOSAIC intervention for this 6-week trial

Although the E-MOSAIC incorporates a module offering the possibility for real-time measurement of clinical benefit response and showing it in the LoMoS the duration of this study of 6 weeks treatment, classical clinical benefit response will not be measured as an outcome, since it needs longer observation to fulfill the criteria.

### Patient population and setting

Patients are eligible who receive anticancer treatment in palliative intention given weekly or biweekly or continuous in the outpatient setting, and routine care which typically includes weekly visits. The setting and routine processes of care include a personal professional nursing contact and a brief patient assessment before the patients visit at the oncologists.

• The palliative intention of the anticancer treatment is defined as an expected tumor response rate ≤ 20% according to literature. To operationalize this definition, a list of tumor types and treatment line was composed (e.g. second line non-small cell lung cancer).

• Patients have to be symptomatic (symptoms measured by VAS: 0 = best, 10 = worst; average over last 24 hours) by the cancer disease, defined as at least one ESAS symptom > = 3/10.

• Patients have to be able to understand the language of the E-MOSAIC assessment and the study related information, written informed consent and the physician is able to communicate with the patient studied without major difficulties (i.e., culture, language, speech).

### Eligible oncologists

Participating oncologists need to be

• experienced in medical oncology and working in a study center or practice, who are likely not to change standard of care for symptom assessment or for major communication skills and who are likely to stay in the participating institution for the time required to treat at least 5 study patients;

• authorized to communicate with the patient about all aspects of cancer care and be authorized to independently perform immediate changes of interventions in patient care without the institutional requirement to counsel another colleague before prescriptions;

• familiar with communication skills, defined as completion of a basic communication skills course or an equivalent training.

### Trial design

A cluster-randomized 2-arm design is used to test the E-MO*S*AIC intervention with the LoMoS given to physicians. At enrolment each participating physician will be randomly allocated to one of the 2 arms (standard care, E-MO*S*AIC + LoMoS) at 1:1 ratio stratified according to the institution. All eligible patients to be treated by the physician will be under the same intervention (Figure 3).

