**Figure 3 F3:**
[figure not shown]
Randomization with intervention.

After the registration, the palm will recognize the oncologist (scroll bar) and automatically provide the software for the control or the E-MO*S*AIC arm, respectively. After synchronization the unique patient number (UPN) will be updated immediately, with maximal 12 patients per oncologist only 12 patient-UPNs will be possible.

This trial design was chosen in order to minimise contamination. Several patients allocated to the same physicians can hardly be considered independent. In particular, a physician familiar to the LoMoS intervention would probably treat his patients in a similar way, even if they were randomized to different interventions. To prevent this contamination, physicians are chosen as clusters [29]. Cluster randomisation is a standard approach to evaluate both process outcomes and patient outcomes, and is considered especially relevant if the intervention is on physician level and outcomes are patient reported [30].

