### Sample size calculation

Sample sizes are calculated for an inequality test for two means of change in QoL in a cluster randomized design using the software package NCSS 2004 - PASS 2002, according to the formulation of Donner and Klar, assuming a two-sided significance level of 0.05, and a statistical power of 0.8 [40]. Further assumptions on design parameters are an overall variance (s2) of 400, an intracluster correlation coefficient (ICC, estimated by the ratio of between-cluster variation to overall variance) of 0.05 , an effect size (between-arm difference in G-QoL to be detected) of 10, and the cluster size (the number of evaluable patients per physician) [40]. For the cluster size several options are considered, but it is expected to stop the trial at a cluster size of 8 with 12 physicians per arm, yielding a total sample size of 192 evaluable patients.

Since the initial estimate of the ICC might not be appropriate, an interim analysis to adjust the sample size as suggested in Lake et al. is foreseen [41]. Once data for the first 100 patients are available, estimates of within-cluster variation and between-cluster variation are obtained. If the resulting ICC has to be at least 1.5 times larger than the value taken for the initial sample size estimation, then the sample size would be adjusted using the new estimate of ICC, without alteration on other design parameters. The feasibility of patient accrual is evaluated at the same time. The recommended cluster size might be adjusted accordingly.

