### Data analysis

Due to the cluster structure, comparisons of different outcomes between treatment arms will be analyzed by mixed models. For endpoints with continuous values, linear mixed model may be applied. For endpoints with categorical or binary values, nonlinear mixed model or generalized estimating equations may be applied.

The data will be stored and analyzed at the SAKK Coordinating Center using SAS software, Version 9.2 of the SAS System for Windows (SAS Institute Inc., Cary, NC, USA) and the open source R statistical software package (http://www.r-project.org/). All statistical tests will be done two-sided at a significance level of 0.05. P-values will be corrected for multiple testing where appropriate.

Descriptive statistics will be done by median and range for continuous variables. Categorical data will be reported using absolute and relative frequencies.

For the *primary endpoint*, selected influential variables (education, tumor type, predominant symptom, anxiety, complexity, hospitalisations) and the baseline G-QoL value will be included in the analysis model as covariates. For the primary analysis, only evaluable patients will be used. As a sensitivity analysis, non-evaluable patients will be included if possible. For instance, the difference between baseline and 3 weeks will be analyzed including patients who are evaluable at week 3 but non-evaluable at week 6.

Several pre-defined subgroup analyses are foreseen: The difference in G-QoL will be compared between both arms in sub-groups of patients having

a) a tumor size response (SD, PR, CR) or not (PD),

b) basic education or additional education

c) one of the main tumor types defined as composing > = 20% of the evaluable study patients.

d) a predominant symptom, if composing > = 20% of the evaluable study patients (expected based on symptom epidemiology data: pain, anorexia and/or fatigue [both predominant vs. other symptoms or alone vs. other symptoms], anxiety and/or depression [both predominant vs. other symptoms or alone vs. other symptoms], nausea, shortness of breath).

e) anxiety <6/10 or > =6/10

f) complexity less than 3 symptoms above threshold vs. > = 3 symptoms above threshold (fatigue and anorexia > =9/10, other symptoms > =6/10).

All subgroup analyses will include baseline G-QoL as covariate.

The study population will be described separately by institution (study center)-, oncologist-, and patient-related factors.

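### Institution stratifies the randomisation but is not in the stated primary model; if institutions differ, the test is mildly conservative and a little power is forgone

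*Protocol article*

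**What the plan says.** Under Trial design, each physician is to be "randomly allocated to one of the 2 arms (standard care, E-MO*S*AIC + LoMoS) at 1:1 ratio stratified according to the institution". The text after Figure 3 explains that "physicians are chosen as clusters" in order to limit contamination.

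Under Data analysis, the general rule is: "Due to the cluster structure, comparisons of different outcomes between treatment arms will be analyzed by mixed models". For the primary endpoint the article then gives an explicit adjustment list: "selected influential variables (education, tumor type, predominant symptom, anxiety, complexity, hospitalisations) and the baseline G-QoL value will be included in the analysis model as covariates". Institution is not on it. The same section gives institution one role only, a descriptive one: "The study population will be described separately by institution (study center)-, oncologist-, and patient-related factors". No institution term, fixed or random, is stated anywhere in the article, and the random part of the mixed model is not spelled out.

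**The concern.** Stratifying by institution makes the two arms similar in their mix of institutions, so differences between institutions largely drop out of the true sampling variance of the arm difference. A model with physician as its only grouping level does not know this. It puts any institution differences into the between-physician variance, which is the error term for the treatment effect. The reported standard error is then too large, the confidence interval too wide and the test conservative, and the precision gained by stratifying is not used.

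The article gives some reason to think that institutions could differ. Approvals come from eight cantons, the tool exists in three languages, and assessment procedures and available symptom interventions are recorded for each centre because they are local.

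**Working it through.** **Inputs.** From Sample size calculation: variance 400, ICC 0.05, difference 10, "assuming a two-sided significance level of 0.05, and a statistical power of 0.8", and 12 physicians per arm with 8 patients each. From Interim analysis: 20 physicians per arm with 4 patients each. Assumed, because the article does not give it: the share s of the between-physician variance that lies between institutions, shown over its full range. Also assumed: equal clusters, exact balance within institution, and 8 institutions (the number of cantons named) when counting degrees of freedom for a fixed factor.

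**1. The plan's own sizes.** With k physicians per arm and m patients each, the variance of the arm difference is 2 × 400 × [1 + (m − 1) × 0.05] / (k × m).
- 12 × 8: 800 × 1.35 / 96 = 11.25. The noncentral t with 22 df gives power 0.813.
- 20 × 4: 800 × 1.15 / 80 = 11.5. The noncentral t with 38 df gives power 0.820.

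These are the smallest k that reach 80% for those cluster sizes, so the stated totals of 192 and 160 are both reproduced.

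**2. True variance under stratification.** With balance within institution, the institution part cancels: 800 × [0.95 / (k × m) + 0.05 × (1 − s) / k]. A model without institution still estimates roughly the variance in step 1. For 20 × 4:
- s = 0: 11.5; SE ratio 1.00
- s = 0.5: 800 × (0.011875 + 0.00125) = 10.5; SE ratio √(11.5/10.5) = 1.047
- s = 1: 800 × 0.011875 = 9.5; SE ratio √(11.5/9.5) = 1.10

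**3. Alpha and power.** Without institution, the critical value is in effect multiplied by the SE ratio, while the estimate itself has the smaller true variance. Both must enter the power. With fixed institution effects, the correct SE is used and 7 df are given up.

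| Design, ICC 0.05 | s | SE overstated | True alpha | Power without institution | Power with fixed institution |
|---|---|---|---|---|---|
| 20 × 4 per arm | 0 | 0% | 0.050 | 0.820 | 0.815 |
| 20 × 4 per arm | 0.5 | 5% | 0.041 | 0.830 | 0.848 |
| 20 × 4 per arm | 1 | 10% | 0.032 | 0.841 | 0.881 |
| 12 × 8 per arm | 0 | 0% | 0.050 | 0.813 | 0.796 |
| 12 × 8 per arm | 0.5 | 8% | 0.035 | 0.830 | 0.855 |
| 12 × 8 per arm | 1 | 19% | 0.022 | 0.851 | 0.913 |

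On a normal approximation that charges no df, the 20 × 4 comparison is about 0.85 against 0.87 (s = 0.5) and 0.86 against 0.90 (s = 1): again 2 and 4 points.

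Simulation (20,000 runs each) of 10 institutions × 4 physicians × 4 patients and 6 × 4 × 8 agrees. At ICC 0.05 and s = 1, rejection under the null without institution was 0.033 and 0.026. Power without and with institution was 0.838 and 0.877 for the first layout, and 0.851 and 0.916 for the second.

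**4. If between-cluster variance is nil.** At ICC 0, the case nearest to the interim result, power without and with fixed institution is 0.869 and 0.865 (20 × 4), or 0.911 and 0.899 (12 × 8). Nothing is gained.

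**The case against.** The strongest objection is that the effect is conditional and the trial's only observed ICC argues against it. Institution variance is part of between-physician variance, the interim ICC was negative, and the article reads that as negligible variation between clusters. This carries weight, but it does not settle the matter. The estimate rests on 81 usable patients (89 − 8) under 23 physicians (31 − 8), about 3.5 each. The usual large-sample formula, (1 − ρ)[1 + (m − 1)ρ]√{2 / [m(m − 1)(k − 1)]} with k here the 23 physicians, gives a standard error of about 0.11 at ρ = 0.05. A negative estimate is therefore compatible with the planning value.

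Other parts of the objection stand:
- The listed covariates may already absorb much of the case-mix difference between institutions.
- Many clusters had one, two or no patients. Balance within institution is then looser, the cancellation incomplete and the conservatism smaller than in the table.
- The case s = 1 requires no physician variance within institutions, which fits poorly with the article's reason for clustering by physician.
- The full protocol or analysis plan may contain a random institution effect that the article does not report.

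A reader might go further and infer that power is certainly lost, or that the same omission affects every secondary comparison. The article supports neither. It gives no between-institution variance, and it does not set out the models for the secondary endpoints in enough detail to show an omission there.

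**Conclusion.** The mismatch is real: the factor that constrains the randomisation is absent from an explicit adjustment list for the primary endpoint. The consequence is small and depends on institutions differing after adjustment. For 20 physicians per arm with 4 patients each at ICC 0.05, the SE is overstated by 0 to 10%, alpha lies between 0.050 and 0.032, and 0 to 4 power points are forgone. For the earlier planned 12 × 8 layout the upper ends are 19%, 0.022 and about 6 points.

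This is not a validity problem. The error is on the conservative side, so type I error is not inflated. Nor is the trial underpowered for this reason: at the planning ICC, power without institution is at least 0.81 in every case, because the sample size formula took no credit for stratification. What is forgone is precision above the target. The figures assume equal clusters and balance within institution, and given the interim ICC the actual loss may be near zero. The point is a free improvement, not a required correction.

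**What to change.** State in the plan that institution enters the primary mixed model, or give the reason for leaving it out. The preferred form is a random institution effect above the physician effect, which keeps institutions with only one physician. The alternative is a fixed stratum factor with the smallest sites pooled under a rule set in advance. If the full plan already has such a term, saying so is enough.

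The change is to analysis wording only. A fixed factor uses a few degrees of freedom: 7 with 8 institutions, although the article lists cantons and does not count institutions. If institutions do not differ, that costs about 0.5 points (0.820 to 0.815 at 20 × 4) to 2 points (0.813 to 0.796 at 12 × 8, just under the target). A random effect should cost less, but this was not calculated.
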